### Additional analyses

Data collected in the present study will provide ample opportunities to answer many different research questions. It is not possible to describe all potential research questions in detail, but we will highlight some of them here. First, the above-described procedure relates to pleasure scores but a similar approach can be followed to investigate changes in specific lifestyle behaviors, to answer the question to what extent each of the interventions induced health-related behavioral change.

Second, another goal with regard to the secondary study parameters is to examine whether the levels of specific biomarkers (e.g., dopamine, BDNF) are associated with the momentary pleasure levels. This will be investigated by conducting multilevel analyses with three levels: the assessment level (Level 1), the month level (Level 2), and the individual level (Level 3). In this way, we can explore how levels of these specific biomarkers are cross-sectionally and prospectively associated with momentary pleasure levels and changes therein. This design will allow to examine whether and how the level of biomarkers measured at the beginning of a month are predictive for the momentary pleasure levels experienced during that month.

Finally, the survey data (*N* = 2000) can be used in order to elucidate the various faces of pleasure loss (i.e., in different domains and dimensions), and how often and in which combinations they occur among young adults. This will be done by conducting latent class analysis. In latent class analysis, it is possible to examine whether individuals can be grouped according to their pattern of pleasure loss. Further, when different groups of individuals are found, we will be able to predict group membership, by examining whether different variables increase the odds of being in a particular anhedonia group.

### Missing data

Participants are required to complete at least 80 % of the momentary assessments each month to be included in the analyses. Participants who complete less than 80 % in the first month, will be excluded from the study. Attrition analyses will be conducted to compare these drop-outs with the participants on demographic characteristics and levels of pleasure. Missing data will be imputed by means of Expectation-Maximization imputation.

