**Methods:**

Our study design is an exploratory intervention study, preceded by a cross-sectional survey as a screening instrument. For the survey, 2000 young adults (18–24 years old) will be selected from the general population. Based on survey outcomes, 72 individuals (36 males and 36 females) with persistent anhedonia (i.e., more than two months) and 60 individuals (30 males and 30 females) without anhedonia (non-anhedonic control group) will be selected for the intervention study. The non-anhedonic control group will fill out momentary assessments of pleasure and lifestyle behaviors three times a day, for one month. The anhedonic individuals will fill out momentary assessments for three consecutive months. After the first month, the anhedonic individuals will be randomly assigned to (1) no intervention, (2) lifestyle advice only, (3) lifestyle advice plus tandem skydive. The personalized lifestyle advice is based on patterns observed in the first month.

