**Fig. 1 Fig1:**
[figure not shown]
Flowchart of the study design

After the pre-intervention observation month, the anhedonic participants will be randomly assigned (stratified on gender) to: (1) no intervention; (2) personalized lifestyle advice, based on association patterns observed in the first month; or (3) personalized lifestyle advice followed by a tandem skydive. After the second month, at the start of the third month, all participants are free to choose whatever they prefer, regardless of the intervention received after the first month: no intervention, lifestyle advice, or lifestyle advice and a tandem skydive. This last month is added to provide a more realistic impression of the feasibility and appeal of the interventions.

Before and after each observation/intervention month as well as after 6 months and one year (in total 6 times), the participants in the anhedonic groups will fill out an online questionnaire. We will collect blood samples along with the monthly and follow-up questionnaires, i.e. six times per person in total. Before and after their first skydive, participants will be asked to donate a total of four saliva samples. Saliva will be collected by means of salivettes, on which the participant has to chew. A member of the research team will provide the salivettes to the participants and provide instructions on how to use them. The salivettes will be collected by the same research member and transported to the UMCG lab.

The anhedonic intervention groups receive 75 Euro after the observation month; another 125 Euro after the first intervention month; and 200 Euro after the second intervention month. They will receive these incentives only if they reach the required compliance rate of 80% within the required time frame, if they fill out all monthly assessments and provide the required blood samples. For the two follow-up measurements they will receive 50 Euro per measurement, once assessments are filled out and blood samples are provided. This means that anhedonic participants will receive up to 500 Euro in total.

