### Treatment

#### Personalized lifestyle advice

Based on diary observations during the observation month (i.e., three measures per day during 30 days) candidates will receive personalized lifestyle advice. The focus will be on lifestyle behaviors that can potentially be influenced (for exact questions, see Table 2), such as physical activities, diet, sleep, smoking and/or alcohol use, and social contacts. The advice will consist of three main parts. In the first descriptive part of the advice, general information will be presented about the participant’s average levels of lifestyle behaviors and pleasure during the observation month. In the second part, a personalized network model of the mutual relationships among momentary self-reported pleasure and lifestyle behaviors will be constructed to provide insight into temporal, potentially causal, patterns. In this part, only the lifestyle behaviors that show sufficient variability to be informative will be included. To create the personal networks, we will use Vector Autoregression (VAR) and Autoregressive Moving Average (ARMA) analyses. In the third part, we will compare participant’s average levels of lifestyle behaviors to normal population levels as observed in our own screening data as well as data from previous cohort studies in the same age group (e.g., TRAILS, [50]), in order to provide insight in plausible candidates for lifestyle changes. Based on the information presented in the previous parts, a selection will be made of the two or three lifestyle behaviors that bear the most promise for inducing pleasure, and this will be translated into a personalized lifestyle advice. Each participant will be advised to change at least two and at most three lifestyle behaviors. If possible, the advice will be based on the personalized network model described above, as this provides information about causal relationships between lifestyle behaviors and pleasure that are specific for this person. In case of too few variables in the model (i.e., too little variation in lifestyle variables) or no clear associations with pleasure, we will base the advice on the comparisons with norm levels. The advice will be discussed with the participants in person, based on a written report which participants are allowed to take home.

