### Statistical analyses

#### Primary outcome variables

First, we will examine individual response patterns by means of (interrupted) time series analysis (ITS) to detect time trends in the amount of pleasure experienced during the study, and differences in the level and slope between pre- and post-intervention pleasure levels. Interrupted time series analysis is particularly useful to test changes in outcome rates in time periods before and after implementation of an intervention designed to change the outcome (see, for instance, [53]). The number of individuals who show a significant improvement in pleasure in the second month of the study period as compared to the first one will be compared across the three intervention groups to assess to what extent this improvement, if any, is likely to be due to spontaneous recovery or the mere daily registration of pleasure and activities, to the personalized lifestyle advice, or to the tandem skydive experience. In addition, we will explore whether changes in pleasure scores from pre- to post-intervention differ between the three intervention groups in a multilevel model. We will compare both (a) individuals who did and did not receive lifestyle advice; and, within the group who received lifestyle advice, (b) individuals who did and did not perform a skydive. We will use a multilevel model with two levels, in which Level 1 represents the momentary assessments, and Level 2 the individual level (e.g., intervention group). The main advantage of multilevel analyses is that it takes the nested structure of the data into account. By conducting multilevel analyses, we will be able to compare post-intervention mean levels of momentary pleasure between the three intervention groups, while controlling for the level of pleasure in the pre-intervention period (i.e., the observation month).

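### The 80% diary rule also applies after randomisation, so it removes randomised participants from the month-2 arm comparison on the basis of post-allocation compliance

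*Protocol article*

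**What the plan says.** The Missing data section of the protocol article sets two rules. The general one asks for at least 80% "of the momentary assessments each month to be included in the analyses". The second concerns month 1 only: people below 80% "in the first month, will be excluded from the study". The section then plans a comparison of the drop-outs with the participants on demographics and pleasure, and Expectation-Maximization imputation of missing data.

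The timing comes from the Procedure section: "After the pre-intervention observation month, the anhedonic participants will be randomly assigned". Months 2 and 3 therefore follow allocation, and in month 3 participants may choose any of the three options whatever their assigned arm. The Abstract confirms three months of diaries for the anhedonic group.

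Under Primary outcome variables, the first analysis counts people with a "significant improvement in pleasure in the second month of the study period as compared to the first one" and compares the counts across the three arms. The second is a two-level model of post-intervention pleasure that controls for pleasure in the observation month. The Randomization section states that neither participants nor the research team can be blinded.

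**The concern.** Randomisation makes the three arms comparable as allocated. A filter on behaviour after allocation does not preserve that. Here the filter is completion of the same diary that supplies the outcome, in an unblinded trial whose arms range from no intervention to advice plus a skydive. If completion depends on the arm and on pleasure, the arms retained in the analysis differ for reasons other than treatment effect.

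The Background calls the study a superiority randomised trial, and Strengths and limitations relies on the randomised design to separate the interventions from mere registration. The rule weakens that argument. It also reduces the number of people, and there are at most 24 per arm.

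**Working it through.** **1. Which exclusions come after allocation?** Month 1 precedes randomisation, so exclusion for low month-1 compliance, applied before allocation, does no harm to the arm comparison. The general rule refers to every month and is stated apart from the month-1 rule, so it reaches months 2 and 3. No other section of the article provides for an analysis of all randomised participants.

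**2. The threshold.** Personalized lifestyle advice gives "three measures per day during 30 days", so 3 × 30 = 90 diaries a month and 0.80 × 90 = 72. A person with 71 is out. For comparison, the Sample size calculation section cites 12 observations before and 12 after for time series, and 20 Level 1 cases for the multilevel model.

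**3. The plan's own sample size.** The article states 21 per group for the monthly questionnaires (d = 0.8, correlation 0.6, power 0.8, alpha 0.05, taken as two-sided). With change-score variance factor 2(1 − 0.6) = 0.8, the normal approximation is 2 × ((1.960 + 0.842)/0.8)² × 0.8 = 19.6, or 20 per group. The noncentral t version gives 21 (power 0.807), which reproduces the stated figure. On the same calculation, power is 0.858 with 24 per arm, 0.787 with 20, 0.715 with 17 and 0.657 with 15. This calculation concerns the questionnaires, not the diaries, and serves here only as a scale for lost people.

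**4. How many people the rule could remove.** The plan allows for a fall from 24 to 20 per arm, 4/24 = 16.7%. The article gives no pass rates. Assuming 72 randomised (12 blocks of six) and a pass rate q that is independent across months, 72q remain if only month 2 counts and 72q² if months 2 and 3 both count:

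| Assumed q | Month 2 only | Months 2 and 3 |
|---|---|---|
| 95% | 68.4 | 65.0 |
| 90% | 64.8 | 58.3 |
| 85% | 61.2 | 52.0 |
| 80% | 57.6 | 46.1 |

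The target is 60. At 90%, it is missed only if month 3 also counts.

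**5. Size of bias (assumed inputs).** Let the true effect be zero, the outcome have SD 1, and latent compliance be normal with correlation ρ to the outcome. If the most compliant fraction p of an arm is kept, its mean shifts by ρ × φ(z)/p, where z is the (1 − p) normal quantile. The bias is the difference in shift between arms.

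- Retention 90% and 70%: φ(z)/p is 0.195 and 0.497, difference 0.302. With ρ = 0.2 to 0.5 the bias is 0.06 to 0.15 SD.
- Retention 85% and 75%: 0.274 and 0.424, difference about 0.149. The bias is 0.03 to 0.08 SD.
- Equal retention with the same ρ in each arm: 0.

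With positive ρ, the arm that loses more people looks better. With negative ρ, it looks worse.

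**6. What the rule buys in the multilevel model.** The variance of a person's mean is ICC + (1 − ICC)/n_eff, with n_eff ≈ n × (1 − 0.3)/(1 + 0.3) for an assumed lag-1 autocorrelation of 0.3. At an assumed ICC of 0.4, 90 diaries give 0.4 + 0.6/48.5 = 0.412 and 45 diaries give 0.4 + 0.6/24.2 = 0.425, so 45 diaries carry about 97% of the information of 90 (30 diaries: about 94%; 71 diaries: about 99%). At ICC 0.2, 45 diaries carry about 93%. This concerns precision only and takes the missed diaries as unrelated to pleasure.

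**7. The individual series differ.** Assume a shift of 0.4 within-person SD, independent errors and a two-sided 5% test. With 90 diaries in each month, the standardised shift is 0.4/√(1/90 + 1/90) = 2.68, power about 0.77. With 90 and 12, it is 0.4/√(1/90 + 1/12) = 1.30, power about 0.26. Series length strongly affects who is counted as improved.

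**The case against.** The strongest reply concerns month 3. A reader might infer that a lapse in month 3 certainly removes a person from the month-2 comparison. The article does not establish that. The sentence can be applied month by month, payments are tied to 80% for each month separately, and the primary comparison uses only months 1 and 2. The month-3 effect follows from the literal wording and is best treated as an ambiguity to be closed. Under the milder reading, month-2 compliance still selects the month-2 comparison.

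Second, a reader might take 0.15 SD as the expected bias. It is the top of an assumed range. The model adjusts for month-1 pleasure and the individual analysis is within person, so selection on stable low pleasure is partly removed. The same payment conditions hold in all three arms, practical help with diaries is offered, and the no-intervention arm may choose advice and a skydive in month 3. All of this may narrow differences in compliance, but none of it ensures that compliance is unrelated to arm.

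Third, a reader might conclude that 80% serves no purpose and that the cited 12 observations could replace it. For the individual series this does not follow: step 7 shows that short series would lower the count of improvers in a less compliant arm. A completeness floor has a real rationale there.

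The plan's other provisions do not repair the exclusion. The drop-out comparison is descriptive, is not specified by arm, and follows directly on the month-1 exclusion. Imputation does not reach people who are outside the analyses. The exploratory label tempers the consequences but does not remove the selection.

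**Conclusion.** The point holds for month 2 from the text alone: a stated rule excludes randomised participants from the arm comparison on a post-randomisation variable. For month 3 it holds only on the literal reading.

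The size and direction of bias cannot be determined from the article. The range of about 0.03 to 0.15 SD rests on retention differences of 10 to 20 percentage points, correlations of 0.2 to 0.5 and no baseline adjustment. It is zero if retention and the correlation are the same in all arms. The claim that the rule gains little applies to person means in the multilevel model under the assumed ICC and autocorrelation, and does not extend to the individual time series. The rule defines who enters the primary group comparison, so it should be corrected before analysis.

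**What to change.** - Apply the 80% rule as an eligibility criterion on month 1, before randomisation, and nowhere else as a condition for the group comparison.
- In the multilevel model, include every randomised participant with any month-2 diary, by assigned arm, adjusting for month-1 pleasure.
- State that month-3 compliance does not affect the month-2 comparison.
- Keep the set with at least 80% as a sensitivity analysis, and report post-randomisation losses by arm, including people with no month-2 diary.
- For the individual responder count, a completeness floor may stay. Report how many randomised participants fall below it in each arm, and do not simply replace 80% with 12 observations.

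The cost is slightly more analysis work and some person-level means that are less precise. No change to data collection is needed. Including sparse diaries does not by itself cure missingness that depends on pleasure within the month, which is why the losses by arm and the sensitivity analysis are needed.

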## Discussion

This study protocol describes a two-phase exploratory intervention study, in which the effects of personalized lifestyle advices and tandem skydives are examined. We hypothesize that providing anhedonic young adults with a personalized lifestyle advice will increase their pleasure levels. Further, we hypothesize that a tandem skydive can reboot the reward system, which would lead to further increases in pleasure, above the effects of the lifestyle advice.

### Strengths and limitations

The study has several strengths. First, it is the first study to explore the effects of a personalized lifestyle advice and a tandem skydive, and hence can provide new insights in effective treatments for anhedonia. Second, as we assess pleasure and lifestyle behaviors in real life and the advices are tailor-made, we ensure that the advices are relevant to each individual. Third, the long period of momentary assessments (i.e., three months) will enable us to explore individual differences in the effects of the interventions and to examine whether differences between groups are due to non-specific intervention effects (e.g., an upward trend that was already present in the observation period). Fourth, by using a randomized design, we will be able to compare whether the lifestyle advice and tandem skydive are more effective in increasing pleasure than only registering one’s emotions and daily life activities.

Despite these strengths, there are also limitations. First, although we follow general recommendations with regard to sample size, we may not be able to detect subtle differences between groups. However, because of the large number of momentary assessments we will be able to detect differences between groups on momentarily assessed outcome variables, and our individual analyses will enable us to determine whether further examination of these interventions in larger samples is likely to be fruitful. Second, as we need to include participants who may be willing to perform a tandem skydive, the generalization of our findings may be limited. We will check in the analyses whether this is indeed the case, by comparing the group of anhedonic individuals that is willing to perform a skydive with the group that is not willing to perform a skydive on demographic characteristics and main study variables. Third, although including more than three measures per day is not feasible due to the long duration of the study (i.e., three months), we might miss some information about lifestyle behaviors and associated pleasure due to the 6 h intervals between assessments. If the intervention proves to be effective, further research examining the effects of lifestyle advices could include more assessments per day, over a short time span (e.g., one month).

### Clinical implications

Findings from the present study could lead to improved treatment for anhedonia. As recent research indicates that it is possible to automate personalized feedback [54, 55], the proposed intervention could be easily implemented in clinical settings, if proven effective. The results from the individual models could lead to additional insights in what works for whom, which could provide starting points for personalizing treatment. Further, if the tandem skydive is found to be effective and pending replication of these potential positive effects, a tandem skydive could be considered as an addition to treatment-as-usual.
